| Statistical Methods:  Statistical Methods (cont’d.) | Demography: descriptive statistics will be provided.  Vaccine reactogenicity: Analyses concern graded severities for local and systemic reactogenicity: Comparing one group with another during a treatment period (the design has two periods following the first and second test article exposures), these are two-sample, cross-sectional comparisons of binary, ordinal, or continuous data. Comparing a group with itself between periods, these are paired, repeated measures data. Two-sample, cross-sectional comparisons are based on Fisher’s exact and Cochran-Mantel-Haenszel tests for binary and ordinal outcomes, respectively. Student’s-t and Wilcoxon tests are used for continuous outcomes. These methods permit statistical tests to address the following topics:   - 1. comparison of active and placebo after test article dose 1   2. comparison of active and placebo after test article dose 2, with and without testing for the impact of, and adjustment for, outcomes after dose 1   3. comparison of active and placebo in successive test article doses   4. comparison of placebo in successive test article doses   5. comparison of change from active to active with change from placebo to placebo   Items c. and d. are paired comparisons, which may be performed by McNemar tests or, more flexibly, by GEE models with a binary or continuous outcome. Items b. and e. are tests of interaction: dose 1 by dose 2 in item b., and period by vaccine in item e. and also accessible by GEE models.  Adverse events: Adverse events will be tabulated by body system using the COSTART dictionary, by severity, by seriousness, by relationship to study drug, and by elapsed time since last exposure to study drug. This yields primarily binary data (for each subject, the given COSTART event did or did not occur) which may be analyzed in the same manner as the binary reactogenicity events.  Vital signs & clinical laboratory measures: Mean values and S.D.s will be plotted separately by treatment group. Extreme values and/or outliers will be discussed individually. For clinical laboratory measures within cross-over groups, quantitative outcomes at baseline and day 28 will be compared by paired Student’s t-tests and Wilcoxon signed rank tests. Binary outcomes will be compared by McNemar’s tests.  Immunogenicity: Immunogenicity measures will include serum hemagglutination-inhibiting (HAI) antibody titers specific for the strains included in the vaccine, levels of secretory IgA (sIgA) specific for these viruses in nasal wash fluids. For the HAI titers, analyses will concern geometric mean titers (GMT), proportions of subjects with titer ≥ 40, and proportions with  four-fold increase over baseline. For specific sIgA levels, analyses will concern geometric means and fold-rise from baseline. HAI GMTs and geometric mean nasal specific sIgA levels will be accompanied by 95% confidence intervals. Comparing active-to-placebo and active-to-active groups, titers/antibody levels will be contrasted on day 28 by t-tests on log10(titer). Within the groups, paired tests will be used (Student’s t and Wilcoxon signed rank). Fold-rises may be examined with and without covariate-adjustment for previous titers. Without such adjustment, there are two binary fold-rise outcomes, and these are compared within and between groups by chi-square and stratified chi-square tests. (In the latter case, 2 x 2 tables of treatment by outcome are stratified by previous titers.) With covariate adjustment, the fold-rise outcome is the log10-ratio of early and later titers. Adjustment after the first treatment is for pre-treatment titer and adjustment after the second treatment is for both baseline titer and for titers after the first treatment.  Response to viral challenge: The analysis concerns between-group comparisons of the three groups regarding clinical and immunologic binary outcomes. Alternative definitions provide six binary clinical outcomes that can be compared between groups by chi-square tests. More flexible analyses use logistic regression (with the presence or absence of illness, separately for each definition, as the outcome. Covariates are cross-over study group, age, gender, race, and, for some models, titers after vaccinations 1 and 2.  Additional analyses will be based on illness score and on virus shedding assessed by two methods: peak and a time-weighted average calculated as a trapezoidal-rule AUC. For both peak and AUC, viral shedding is in units of log10(titer). These continuous data will be compared between cross-over groups by Student’s t-tests and Wilcoxon tests and, in a more flexible analysis, by linear model adjusted for the demographic and clinical covariates cited above.  Finally, the three binary measures of influenza and the two viral load estimates (peak titer and AUC) will be assessed relative to the two immunologic measures, HAI reciprocal titer and nasal secretory IgA. For the binary measures, mean viral load (for each measure) is compared by t-tests between those with and without influenza (for each definition). For the two immunologic measures, the test of association with viral load will be based on Pearson correlations of log-titers. |

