# 9.0 Analysis Plan:

This is a phase II, four-group, placebo-controlled, randomized clinical trial. Approximately 28 subjects will be treated in each group. Volunteers will either receive two 15 µg treatments separated by two weeks, one 30 µg and one placebo treatment separated by two weeks, two 30 µg treatments separated by two weeks, or two placebo treatments separated by two weeks. In the immediate post-treatment period, outcomes are pre-specified local and systemic reactions, general adverse event rates, and immune responses assessed by antibody measurements.

Forty-one (± 3) days after the first treatment, subjects who remain eligible are challenged and then followed for an additional week regarding evidence of illness (by several alternative definitions), and also concerning virologic outcomes.

All analyses will be done with SAS, version 8.2 or later, primarily PROC UNIVARIATE, FREQ, LOGISTIC (for logistic regression with challenge data), and GENMOD (SAS PROC GENMOD implements the repeated measures regression model of Zeger and Liang [48].) Chi-square tests in PROC FREQ are exact. In this phase II trial which will not be used to provide definitive evidence of efficacy or safety, p-values of 0.05 or less for two-sided statistical tests will be considered significant and multiple comparison corrections will not be used (although the rather large number of significance tests – at least as regards safety -makes it likely that the type I error rate will be somewhat elevated.

Simple methods will be used to impute missing data. For binary outcomes, such as the presence/absence of an adverse event, alternative imputations will assume the event did, and did not, occur and the results of these contrary assumptions will be compared. For continuous outcomes, such as antibody titers, last-value-carried-forward will be used except that two consecutive missing values will not be imputed.

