## 9.1 Immunogenicity:

Immunogenicity measures will include serum hemagglutination-inhibiting (HAI) antibody titers specific for the three virus strains included in the vaccine, and levels of secretory IgA (sIgA) specific for these viruses measured in nasal wash fluids. Antibody levels in nasal wash specimens will be assayed by kinetic ELISA and normalized on total content of sIgA. For the HAI titers, analyses will concern geometric mean titers (GMT), proportions of subjects with titer ≥ 40, and proportions with  four-fold increase over baseline. For specific sIgA levels, analyses will concern geometric means and fold-rise from baseline.

HAI GMTs and geometric mean nasal specific sIgA levels will be accompanied by 95%, Student’s t-based confidence intervals. Between active-to-placebo and active-to-active cross-over groups, titers/antibody levels will be compared on day 28 by t-tests on log10 (titer). Within the groups, paired tests will be used (Student’s t and Wilcoxon signed rank).Fold-rises may be examined with and without covariate-adjustment for previous titers. Without such adjustment, there are two binary fold-rise outcomes, and these are compared within and between groups by chi-square and stratified chi-square tests. (In the latter case, 2 x 2 tables of treatment by outcome are stratified by previous titers.) With covariate adjustment, the fold-rise outcome is the log10-ratio of early and later titers. Adjustment after the first treatment is for baseline titer and after the second treatment is for both baseline titer and titer after the first treatment. This facilitates contemporaneous between-group comparisons of placebo and active after both periods 1 and 2.

9.2 Safety:

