### 9.2.2 Immediate Complaints, Vaccine Reactogenicity Complaints, and Standardized Ear, Nose, and Throat Exams:

Immediate complaint data derived from 30 minute post-dose questionnaires will be tabulated for each treatment group by categories of complaints and by severity. Vaccine reactogenicity data derived from memory aids and physician examinations will be similarly tabulated by treatment group, categories of complaints or findings, severity, and duration.

Comparison of graded severities for local and systemic reactogenicity: Comparing one group with another during a period (the cross-over design has two periods), these are two-sample, cross-sectional comparisons of binary, ordinal, or continuous data. Comparing a group with itself between periods, these are paired, repeated measures data. Two-sample, cross-sectional comparisons are based on Fisher’s exact and Cochran-Mantel-Haenszel tests for binary and ordinal outcomes, respectively. Student’s-t and Wilcoxon tests are used for continuous outcomes. These methods permit statistical tests to address the following topics:

- 1. comparison of active and placebo after test article dose 1
  2. comparison of active and placebo after test article dose 2, with and without testing for the impact of, and adjustment for, outcomes after dose 1
  3. comparison of active and placebo in successive test article doses
  4. comparison of placebo in successive test article doses
  5. comparison of change from active to active with change from placebo to placebo

Items c. and d. are paired comparisons, which may be performed by McNemar tests or, more flexibly, by General Estimating Equation (GEE) models with a binary or continuous outcome. Items b. and e. are tests of interaction: dose 1 by dose 2 in item b., and period by vaccine in item e. and also accessible by GEE models.

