### 9.2.4 Vital Signs and Clinical Laboratory Measures:

Mean values for each measure will be plotted separately by treatment group, including ± one standard deviation. Extreme values and/or outliers will be discussed individually. For clinical laboratory measures within cross-over groups, quantitative outcomes at baseline and day 28 will be compared by paired Student’s t-tests and Wilcoxon signed rank tests. Binary outcomes will be compared by McNemar’s tests. This analysis is also vulnerable to elevated type I error.

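### Binary antibody-response outcomes are to be compared within groups by chi-square, although the same subjects stand on both sides; a paired test should be named

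*Protocol*

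**What the plan says.** Section 9.1 of the Protocol analyses HAI responses as geometric means and as two proportions: titer ≥ 40, and at least a four-fold rise. For the binary outcomes without covariate adjustment it states: "there are two binary fold-rise outcomes, and these are compared within and between groups by chi-square and stratified chi-square tests". The Study Synopsis, under Statistical Methods, has the same rule: "these are compared within and between groups by chi-square and stratified chi-square tests". The stratified version is explained as follows: "2 x 2 tables of treatment by outcome are stratified by previous titers".

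Elsewhere the protocol handles repeated data on the same subjects differently:

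- Section 9.1, for titers and antibody levels: "Within the groups, paired tests will be used", with Student's t and the Wilcoxon signed rank test named.
- Section 9.2.2, for reactogenicity: "Comparing a group with itself between periods, these are paired, repeated measures data". For binary outcomes it then says "Items c. and d. are paired comparisons, which may be performed by McNemar tests", with GEE models as the more flexible option.
- Section 9.2.4, for laboratory measures within groups: "Binary outcomes will be compared by McNemar" (that is, by McNemar's tests).

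On size, section 9.0 says "Approximately 28 subjects will be treated in each group". It sets a two-sided 0.05 level and states that chi-square tests in PROC FREQ are exact. The document gives no power, error rate or within-subject correlation for the within-group responder comparison.

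**The concern.** When a responder proportion is compared within one group, the question is whether two proportions measured on the same subjects are equal. An ordinary chi-square test does not address that null hypothesis in either form it could take:

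- **On the two margins.** The 28 subjects are treated as two independent samples of 28. The covariance between the two measurements is left out of the variance, so with positive correlation the test is conservative and loses power.
- **On the subject-level two-by-two table.** The test asks whether the two responses are independent. Rejection then shows that responders tend to stay responders, not that the proportion changed.

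The stratified version does not repair this. Its strata are previous titers, not subjects, and its tables cross treatment with outcome, while treatment is constant within a group.

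At stake are the within-group p-values for responder rates. These bear on objective B in section 2.0, the kinetics and magnitude of the immune response.

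**Working it through.** **Inputs.** From the Protocol: n = 28 per group, two-sided 0.05, exact tests (9.0). Response rates come from section 1.0: 40 to 60% in susceptible subjects in earlier trials, and about 70% in the previous challenge study. The within-subject correlation phi is not given and is varied as an assumption. The plan states no figure for this comparison, so there is none to reproduce.

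**Set-up.** For true proportions p1 and p2 and correlation phi, the four cells of the paired table are

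- p11 = p1·p2 + phi·√[p1(1−p1)·p2(1−p2)]
- p10 = p1 − p11, p01 = p2 − p11, p00 = 1 − p11 − p10 − p01

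All multinomial tables with n = 28 were enumerated. The probabilities of those rejected at 0.05 were summed for exact McNemar (binomial on p10 against p01), Fisher's test on the two margins, and Fisher's test on the paired table.

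**Why pairing matters.** The variance of the difference in proportions is [p1(1−p1) + p2(1−p2) − 2·phi·√(p1(1−p1)·p2(1−p2))]/n. For 0.40 to 0.70 the square root is √(0.24 × 0.21) = 0.2245. The largest possible phi is (0.40 − 0.28)/0.2245 = 0.53. There the numerator is 0.24 + 0.21 − 2 × 0.12 = 0.21, while the unpaired test works with 0.45.

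**Power when there is a true change (unpaired exact / exact McNemar):**

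| phi | 0.40 to 0.70 | 0.40 to 0.60 |
|---|---|---|
| 0 | 0.508 / 0.511 | 0.220 / 0.229 |
| 0.3 | 0.509 / 0.664 | 0.179 / 0.297 |
| 0.4 | 0.508 / 0.745 | 0.162 / 0.337 |
| 0.5 | 0.505 / 0.846 | 0.141 / 0.388 |
| 0.53 (maximum for 0.40 to 0.70) | 0.503 / 0.887 | not run |
| 0.6 | not attainable | 0.118 / 0.450 |

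The relative loss for 0.40 to 0.60 at phi 0.6 is 1 − 0.118/0.450 = 74%. For 0.40 to 0.70 at the maximum it is 1 − 0.503/0.887 = 43%. At phi 0 it is 4% or less in both columns. With no true change, the unpaired test's type I error is about 0.002 at phi 0.5, so the error is towards conservatism.

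**Rejection by the subject-level test when nothing changed (p1 = p2, 0.5 to 0.7):**

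| phi | rejects |
|---|---|
| 0 | 2.5-3% |
| 0.3 | 24-27% |
| 0.5 | 66-67% |
| 0.6 | 84-86% |
| 0.7 | 94-96% |
| 0.8 or more | about 99% or more |

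**A case where nothing is lost.** Entry requires an A/Panama titer ≤ 10 at screening (4.2), so no subject is at ≥ 40 then. Take the baseline as 0/28.

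- With 6 responders later, exact McNemar gives 2 × 0.5⁶ = 0.031, and Fisher on 0/28 against 6/28 gives 0.023.
- With 5 responders, the values are 2 × 0.5⁵ = 0.0625 and 0.0515.

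Both tests therefore need 6 of 28. The subject-level table has an empty margin, so the association test cannot be computed.

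**The case against.** The strongest reply is that the wording is loose rather than wrong. McNemar's statistic is of chi-square type, the same section requires paired tests within groups shortly before, and the passage opens permissively. This has some force, but the earlier sentence lists only tests for continuous or ranked data. The protocol names McNemar elsewhere when it means it, and here one phrase covers both the within-group and the between-group comparison. A programmer following the text would not arrive at a paired test.

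A reader might infer that the planned test almost always rejects, or that it gives up about half its power. The documents do not support either as a fact. Near-certain rejection needs the subject-level form and a correlation of about 0.7 or more. The power loss runs from almost nothing to about three quarters, depending on a correlation that is nowhere stated. The subject-level form is also the less natural reading, since the text speaks of comparing outcomes.

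Three further limits stand:

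- Section 9.1 does not say which within-group contrasts will be tested. A four-fold rise is already a change from baseline, so it has no baseline value to pair with.
- No vaccine dose falls between the Day 28 and Challenge Phase Day 0 samples, and challenge comes after the latter. Nothing in the documents points to a 20- or 30-point change between those visits, so the changes in the power table are illustrative.
- Section 9.0 says the trial will not supply definitive evidence, and no decision rule or sample-size claim rests on this test.

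These points limit the consequence. None of them makes an unpaired chi-square test right for within-subject data.

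**Conclusion.** The point holds as a low-severity error in the choice of test. Sections 9.1 and the synopsis name an unpaired test family for a within-subject binary comparison, at odds with the protocol's own practice for the same kind of data. The size of the harm cannot be fixed from the documents. It is close to nil at zero correlation and grows as correlation rises, either as lost power or, under the association reading, as rejections that say nothing about change. All figures assume 28 evaluable subjects per group, exact tests at two-sided 0.05, and the stated values of phi. Between-group responder comparisons and within-group titer tests are untouched.

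**What to change.** In section 9.1 and in the synopsis, replace the single phrase by two: between groups, chi-square tests with or without stratification by previous titer; within groups, exact McNemar tests (or GEE models, as in 9.2.2). It would help to add which pairs of visits are compared. The cost is one line of wording in two places and a different option in the same SAS procedure. No new data, visits or subjects are needed.

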### 9.2.1 Power and Detectable Effect Size:

In regard to the immediate post-treatment component of the study design, we address the following two questions: What must be the chance of a given reactogenicity event/finding or adverse event in a single subject for there to be a high likelihood (probability 0.80) of a few occurrences in 28(any one treatment group) and 84 (all active treatment) subjects? Secondly, comparing three cross-over groups in the same period, what must be the relative risk of a reactogenicity event/finding or adverse event for the groups to differ significantly in risk? Exact calculations are based on the binomial distribution.

| Chance of an event in a single subject so that there is an 80% chance of at least the given number of events in 28 or 84 subjects | | | |
| --- | --- | --- | --- |
|  |  1 |  2 |  3 |
| n = 28 | 0.056 | 0.103 | 0.146 |
| n = 84 | 0.019 | 0.035 | 0.050 |

Thus, events that occur with probability of about 6% and 2% in a single subject imply an 80% chance of seeing at least one event in, respectively, any given treatment group and all actively-treatment subjects. This phase II study is not intended to be powered to detect rare events.

Turning to comparison of any two cross-over groups, 28 subjects in each, in the same period, we compute the relative risk (RR) that gives 80% power, type I error 5%, to detect RR  1.

| Chance of an adverse event in a placebo vaccinee so that a given risk-ratio yields a significant effect (80% power, 5% type I error) | | | |
| --- | --- | --- | --- |
| relative risk | 5-fold | 3-fold | 2-fold |
| placebo rate | 0.074 | 0.178 | 0.381 |

Thus, for a five-fold relative risk of an adverse event or reactogenicity event, active-to-placebo, to be detectable (with good power), the chances of an adverse event in the placebo group must be 0.074. With a lower adverse event rate among placebo subjects, there would not be good power to detect even a five-fold increase in risk However, for the most frequent reactogenicity events observed with intranasal proteosome-influenza vaccine, mild rhinorrhea and nasal congestion, prior experience indicates that placebo rates will range from 0.2 – 0.3. Thus, there will be adequate power to detect between two- and three-fold increases in risk in active product recipients.

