## 5.1 Immunization Phase:

FluINsure™ will be delivered as one of three different treatment regimens as detailed below in section 5.1.1. In addition, approximately one of every four subjects will receive a placebo control treatment regimen comprising two sequential doses of buffered saline placebo.

The study will enroll up to 112 healthy adult subjects selected for susceptibility to A/Panama/2007/99 into the immunization component.

Healthy normal subjects of both genders and 18 to 50 y.o. will be invited to give informed consent for preliminary screening phlebotomy, and then have a serum specimen obtained for baseline A/Panama/2007/99 HAI antibody testing. Screened subjects with serum reciprocal HAI titers ≤ 10 will be invited to return for a detailed explanation of the clinical trial and asked to give informed consent for participation in the trial itself. Consenting subjects will then undergo an assessment of their medical history, physical examination, ECG, and selected clinical laboratory tests to ensure eligibility according to the protocol. A nasal wash sample for measurement of secretory IgA (nasal sIgA) specific for the vaccine virus strains will be obtained during screening.

5.1.1 Treatments:

Eligible subjects will be randomized, using a gender-specific randomisation list prepared by the Sponsor, to one of four treatment groups in a ratio of approximately 1:1:1:1. The treatment groups will receive:

Treatment Group A) Two intranasal spray doses, each dose containing 15 μg of each of three hemagglutinins (HA) formulated with proteosomes. The first dose will be given on day 0 and the second given after a 14-day interval.

Treatment Group B) Two intranasal spray doses, the first containing 30 μg of each of three hemagglutinins (HA) formulated with proteosomes, and the second containing buffered saline (placebo). The first dose will be given on day 0 and the second given after a 14-day interval.

Treatment Group C) Two intranasal spray doses, each containing 30 μg of each of three hemagglutinins (HA) formulated with proteosomes. The first dose will be given on day 0 and the second given after a 14-day interval.

Treatment Group D) Two intranasal spray doses of buffered saline. The first dose will be given on day 0 and the second given after a 14-day interval.

All dose volumes will be 0.28 mL (as 0.14 mL per nostril). Each treatment group will include approximately 28 subjects.

5.1.2 Safety and Tolerability Evaluation:

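### Groups B and C have the same exposure until the second dose, but the safety comparisons are sized and described only as 28 against 28; pooling B and C after dose 1 and labelling denominators by dose would sharpen them at no cost

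*Protocol*

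**What the plan says.** Protocol 5.1.1 randomises about 28 subjects to each of four groups, "in a ratio of approximately 1:1:1:1". Group A receives 15 µg twice, C receives 30 µg twice and D receives saline twice. Group B receives 30 µg first, "and the second containing buffered saline (placebo").

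Protocol 9.2.1 gives two tables. The first finds the event probability that yields an 80% chance of at least one, two or three events, in 28 subjects (one group) or in "84 (all active treatment) subjects". No dose or period is attached to the 84. The second finds the placebo rate at which a five-, three- or two-fold risk is detectable, introduced with "Turning to comparison of any two cross-over groups, 28 subjects in each, in the same period". From prior placebo rates of 0.2 to 0.3 for mild rhinorrhea and congestion, the section concludes that "there will be adequate power to detect between two- and three-fold increases in risk in active product recipients".

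Protocol 9.2.2 frames the reactogenicity analysis as "Comparing one group with another during a period (the cross-over design has two periods"), with Fisher's exact test for binary outcomes. It lists active against placebo after dose 1 and again after dose 2, but does not say which groups form the active side in either period. Section 9.0 sets the level: "p-values of 0.05 or less for two-sided statistical tests will be considered significant".

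**The concern.** Until the second dose nothing distinguishes B from C: same product, same dose, same blinding. If the 30 µg dose is compared with placebo as B v D and again as C v D, one exposure is tested twice, each time with half of its subjects. Safety and tolerability are the first objective, and the first-dose contrast with placebo is the cleanest randomised evidence on reactogenicity.

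After dose 2 the number receiving active spray changes. B has had saline, so 56 subjects, not 84, have had an active second dose. A reader who takes the n = 84 row as the chance of seeing a second-dose reaction would be too optimistic. The comparison labelled active against placebo after dose 2 also needs a stated place for B.

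**Working it through.** **Inputs.** About 28 per group and the dose schedule (Protocol 5.1.1); two-sided 0.05 (9.0); Fisher's exact test (9.2.2); 80% power and placebo rates of 0.2 to 0.3 (9.2.1). The midpoint 0.25 is added for illustration.

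**Exposure by dose.**

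| | 15 µg | 30 µg | Saline |
|---|---|---|---|
| Dose 1 | A = 28 | B + C = 56 | D = 28 |
| Dose 2 | A = 28 | C = 28 | D = 28, and B = 28 (already vaccinated) |

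Active at dose 1: 28 + 56 = 84. Active at dose 2: 28 + 28 = 56.

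**Reproducing the event table.** Solve P(X ≥ k) = 0.80 with X ~ Binomial(n, p). For k = 1 this is p = 1 − 0.20^(1/n).

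| n | k = 1 | k = 2 | k = 3 | Protocol |
|---|---|---|---|---|
| 28 | 0.056 | 0.103 | 0.147 | 0.056 / 0.103 / 0.146 |
| 84 | 0.019 | 0.035 | 0.050 | 0.019 / 0.035 / 0.050 |
| 56 | 0.028 | 0.053 | 0.075 | not given |

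The printed rows reproduce, apart from one unit in the third decimal. At n = 56 the thresholds are about 1.5 times those at 84. An event with probability 0.019 is seen at least once with probability 1 − 0.981^56 = 0.66, against 1 − 0.981^84 = 0.80.

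**Reproducing the relative-risk table.** At the printed placebo rates (0.074, 0.178, 0.381 for five-, three- and two-fold), 28 v 28, the exact power of the uncorrected chi-square test is 0.795, 0.821 and 0.834. The table therefore follows approximately from its own sample size under that test. Under two-sided Fisher the same rates give 0.685, 0.744 and 0.760. The comparison below uses Fisher throughout, because 9.2.2 plans it.

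**Effect of pooling at dose 1.** Fisher power is the sum, over all outcome pairs with two-sided p ≤ 0.05, of the product of the two binomial probabilities. D has 28 subjects; the 30 µg side has 28 (one group) or 56 (B + C).

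| Placebo rate | Power for two-fold risk, 28 v 28 | Same, 56 v 28 | Risk ratio at 80% power, 28 v 28 | Same, 56 v 28 |
|---|---|---|---|---|
| 0.20 | 0.28 | 0.41 | 2.94 | 2.61 |
| 0.25 | 0.39 | 0.55 | 2.60 | 2.32 |
| 0.30 | 0.51 | 0.71 | 2.35 | 2.11 |

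**Dose 2.** A v D and C v D remain 28 v 28, so the n = 28 row and the relative-risk table still describe them. If A and C are combined against D, the 56 v 28 columns apply.

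**The case against.** Much of the case against stands.

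- A reader might infer that the protocol assumes 84 active subjects in both periods. It does not: the 84 has no period attached, and it is correct for dose 1 and for subjects ever vaccinated, which is a natural denominator for adverse events followed to day 60–70.
- A reader might infer that the dose-2 figures fail as a whole. They do not: A v D and C v D are still 28 v 28. Only the n = 84 row, if taken as second-dose exposure, and B v D, if taken as active against placebo, would mislead.
- A reader might infer that B will be counted as active after dose 2 and dilute the contrast. With illustrative rates of 50% and 25%, that would give (56 × 0.50 + 28 × 0.25)/84 = 0.42 and a risk ratio of 1.67 instead of 2.0. But 9.2.2 lists a paired comparison of active and placebo in successive doses. Only B can supply this, so the plan treats B's second dose as placebo.
- A reader might infer that the power sentence is wrong because the table needs a placebo rate of 0.381 for a two-fold risk. The sentence speaks of increases between two- and three-fold, and the ratios detectable at 28 v 28 (2.35 to 2.94) lie in that range.
- The text does not forbid pooling B and C, and an analysis plan not shown here may provide for it. Wasted power is therefore not established, and the stated sizing errs on the safe side.

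What remains is that the protocol itself fixes the form of comparison as group against group and sizes it at 28 v 28, while its own schedule supports a larger first-dose contrast. It also prints a single active denominator for a design in which that number changes between doses.

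**Conclusion.** The point holds as an improvement, not as an error in the protocol's figures. Pooling B and C after dose 1 lowers the detectable risk ratio by about 0.24 to 0.33 (2.94/2.60/2.35 to 2.61/2.32/2.11) and raises Fisher power for a two-fold risk by 13 to 20 percentage points at placebo rates of 0.20 to 0.30. For second-dose active exposure, the 80% detection thresholds are 0.028/0.053/0.075.

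These results assume full groups of 28, equal underlying risk in B and C before the second dose (which randomisation and identical exposure justify) and the protocol's placebo rates. Losses before dose 2 would reduce the dose-2 numbers somewhat. The trial is not presented as definitive on safety, and no sample size or decision rule depends on the change.

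**What to change.** - **9.2.2, dose 1:** define the 30 µg reactogenicity contrast as B + C (about 56) v D (28), and the 15 µg contrast as A v D.
- **9.2.2, dose 2:** compare A and C, separately or together (56), with D, and show B separately as active followed by placebo.
- **9.2.1:** label the n = 84 row as dose 1 or ever-vaccinated subjects, and add an n = 56 row (0.028/0.053/0.075) for second-dose active exposure. Keep the n = 28 row, the 28 v 28 comparison for A v D and C v D at dose 2, and the sentence on two- to three-fold increases.
- **9.2.3:** keep B in the ever-vaccinated denominator for adverse events. Removing it after dose 2 would drop 28 vaccinated subjects from follow-up for later events.

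The cost is a few sentences and one table row, settled before unblinding. No subjects, visits or data are added.
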